### Criteria for discontinuing or modifying allocated interventions {11b}

The exercise load will be continuously adjusted to the increased or decreased capabilities of the participants: for HEAVY, the load will increase whenever the participant is able to complete more than the pre-defined repetitions for all sets with acceptable symptoms below 5/10 on a Numerical Pain Rating Scale (NPRS) and good movement quality (defined as no glenohumeral subluxation and no increased or obvious scapula dyskinesis [38] compared with unloaded movement). For LIGHT, the progression will be applied by changing from isometric to dynamic exercises during the 16-week exercise programme, by increasing the intensity of the pressure in isometric exercises and by adjusting the length of the resistance band, while keeping acceptable symptoms below 5/10 on the NPRS and maintaining good movement quality. For both groups, the same modification rules apply if participants experience symptoms or pain flares above the acceptable threshold: the demands of the exercise will be reduced (i.e. load, range of motion, sets and repetitions, number of weekly exercise sessions, and by excluding provoking exercises), if symptoms or pain experienced during the exercise session persist for more than 2–3 h, e.g. until the next day or the next exercise session. The exercises will then be performed at that level until the symptoms decrease below the threshold of 5/10 on the NPRS. Thereafter, increases in load will follow the progression as initially planned. For participants with symptoms at rest above 5/10 at baseline, no increase in symptoms will be allowed during exercise.

### Strategies to improve adherence to interventions {11c}

In REDCap, a dashboard report will be created for both groups to monitor whether the weekly email questionnaire has been answered, as well as evaluating exercise adherence in a question regarding number of completed sessions. In case participants fail to attend a supervised exercise session, the treating physiotherapists will contact them by phone to inform them about the importance of adherence to the protocol. Further efforts will be made to make sure that exercise sessions are scheduled as convenient as possible for participants. If participants fail to complete their exercise sessions for 2 consecutive weeks, they will receive an email with follow-up questions about reasons for non-adherence. Every week, the project manager will briefly look at answers from the weekly questionnaire to make sure there are no adverse events preventing the participants from continuing the exercise programme, and if necessary, she will encourage the participants to remember to perform their exercise sessions.

### Relevant concomitant care permitted or prohibited during the trial {11d}

Participants can take pain medication during the study and continue with existing medical treatments as advised by their general practitioner. Participants will be encouraged to limit concomitant interventions for the shoulder such as manual therapy and other physiotherapy treatments. However, if the participant finds any supplementary treatment necessary to be able to complete the current interventions (e.g. manual treatment for exercise-induced headache), they will be encouraged to receive as few of those treatments as possible and report these concomitant interventions on the weekly questionnaire.

### Provisions for post-trial care {30}

No post-trial care will be provided to the participants. However, participants are not restricted from getting other treatments after the 16-week intervention period.

### Outcomes {12}

#### Primary outcome measure

The primary outcome is self-reported shoulder function measured using the WOSI total score developed for patients with shoulder instability [39]. The main analysis will be conducted for changes from baseline to 16-week follow-up, reported as the difference in mean change between groups. The WOSI has 21 questions, each marked on a scale from 0 to 100, with 0 being the best score (no limitations related to the shoulder) and 100 representing the worst score, with a total ranging from 0 to 2100 points [40]. It consists of four subscales: physical symptoms (10 questions; maximum score of 1000); sports/recreation/work (4 questions; maximum score 400); lifestyle (4 questions; maximum score 400); and emotion (3 questions; maximum score 300). The WOSI is responsive and sensitive to change as well as being a valid questionnaire, with a high test-retest reliability [41]. A Danish-validated digital version will be used [39].

#### Secondary outcome measures

Relevant secondary condition-specific and generic self-reported outcomes and objective measurements will be used in this study (Fig. 2). For these outcomes, the main analyses will be conducted for changes from baseline to 16-week follow-up, reported as the difference between groups in mean change or difference in proportions for continuous and dichotomous outcomes, respectively, unless indicated otherwise.

**Fig. 2 Fig2:**
[figure not shown]
Time schedule of enrolment, interventions, assessments, and visits for participants

##### Secondary self-reported outcomes

Data from each of the four subscales (physical symptoms, sports/recreation/work, lifestyle, and emotion) from the WOSI questionnaire will be reported. Shoulder pain will be measured using the NPRS with numbers from 0 to 10 (“no pain” to “extreme pain”) [42]. The worst, least, and average pain level for the past week will be measured every week. Pain intensity before and after each exercise session will be measured [42]. Assessment of shoulder symptoms other than pain (instability, subluxation, laxity) will be measured in the same way as for shoulder pain by the NRS from 0 to 10 (“no symptoms” to “extreme symptoms”).

To evaluate whether a health condition impacts the patient’s ability to perform activities they nominate as important to them, the Patient-Specific Functional Scale (PSFS) [43] will be used. At baseline, the participant is asked to identify up to three important activities being difficult or impossible to perform due to symptoms. The participant provides a rating for each selected activity, on an 11-point ordinal scale ranging from 0 (“unable to perform activity”) to 10 (“able to perform activity at the same level as before the injury or problem”). During reassessments, the participant is prompted to re-rate the same activities. The average of up to three specific activity scores is recorded, and the range of possible scores is 0–10. Higher scores indicate less impairment.

Assessment of fatigue will be performed with the Checklist Individual Strength (CIS), the subscale of fatigue, which has shown good reliability and validity. The CIS subscale of fatigue consists of 8 items each scored on a 7-point Likert scale (scores ranging from 8 to 56) with high scores indicating high levels of fatigue [44].

To assess functional health status, the Dartmouth Primary Care Cooperative Research Network/World Organization of National Colleges, Academies and Academic Associations of General Practitioners/Family Physicians (COOP/WONCA) questionnaire will be used. The questionnaire is a generic health status questionnaire for general practice patients. The questionnaire consists of six single-item measures: physical fitness, feelings (mental well-being), daily activities, social activities, change in health, and overall health. The categories chosen are scored from 1 (good functional status) to 5 (poor functional status) with total scores ranging from 6 to 30 [45, 46].

Fear of movement is measured using the Tampa Scale of Kinesiophobia-11 (TSK-11), which consists of an 11-item scale where each question is scored on a 4-point Likert scale, with 1 indicating “strongly disagree” and 4 indicating “strongly agree”. The total scores range from 11 to 44, with higher scores representing increased fear of movement [47].

Health-related quality of life is measured with the generic instrument European Quality of life-5 Dimensions-Five-Level Scale (EQ-5D-5L). It is a classification system that comprises five dimensions (mobility, self-care, usual activities, pain/discomfort and anxiety/depression), where each dimension is rated by a five-level ordinal scale as follows: (1) no problems, (2) slight problems, (3) moderate problems, (4) severe problems, and (5) extreme problems [48]. This classification describes 243 unique health states that are often represented as vectors. From population-based studies, societal value sets have been derived and when they are applied to the health state vectors, they result in a preference-based index that ranges from the state worse than death (< 0), to 1 (full health), with anchoring of death as 0. A score of 1 indicates that the patients perceive their health at the best possible state and a score below 0 that the patients perceive their health worse than death [48, 49]. In addition, the EQ-5D includes an EQ-VAS scale where the patient’s own health “today” is rated between 0 (worst imaginable health) and 100 (best imaginable health). In patients with shoulder instability problems, EQ-5D-5L has satisfactory psychometric properties [49, 50].

To measure the patients’ self-reported impression of important health changes, the Global Perceived Effect (GPE) will be used on each of the four WOSI domains (physical symptoms, sports/recreation/work, lifestyle, and emotions). Patients will rate their experienced change and importance on 7-point scales ranging from “worse, an important worsening” to “better, an important improvement” [51, 52]. The main analysis is conducted to compare the self-reported impression at 16-week follow-up between groups.

##### Secondary objective outcomes

Isometric shoulder strength will be assessed by measuring maximum isometric voluntary contraction in shoulder scaption, internal rotation and external rotation using a handheld dynamometer (IsoForce Dynamometer EVO2; Medical Device Solution AG) [53, 54].

Active and passive shoulder range of motion in internal and external rotation with the shoulder at 90° of abduction [53, 55] and shoulder proprioception in shoulder flexion angles (low-range and mid-range) [56, 57] are assessed using a HALO digital goniometer (Halo Medical Devices, Subiaco, Australia).

Shoulder laxity, hypermobility, and instability will be assessed using the anterior and posterior load and shift [58], sulcus sign [58], Gagey [58], apprehension [58], relocation [58], release [58], Rotés Qúerol [59], and shoulder rotation and flexion [60] tests.

#### Other outcome measures

Participants will be evaluated on self-efficacy related to symptoms, which can be defined as an individual’s confidence to successfully produce desirable results related to living with symptoms. The Self-Efficacy Questionnaire has 10 items which are rated on a 7-point ordinal scale (ranging from 0 “not at all confident”, to 6 “completely confident”). The questionnaire is applicable to patients with persistent pain and covers a range of functions including work, socialising, and household chores as well as coping with pain without medication. The maximum score is 60, and the higher the score, the higher the level of self-confidence managing their symptoms [61].

Participant expectations of treatment effectiveness will be evaluated by asking “How much do you expect your shoulder problem to change as a result of physiotherapy treatment?”, measured on a 7-point Likert scale ranging from 1 “worse than ever” to 7 “complete recovery” [61].

The Patient Acceptable Symptom State (PASS) will be used to evaluate patient satisfaction and consists of simple global dichotomised questions about a patient’s satisfaction of their state of symptoms and treatment failure and is adapted from a previous knee study [62]. Participants will be asked: “When you think of your shoulder function, will you consider your current condition as satisfactory? By shoulder function, you should consider your activities of daily living, sport and recreational activities, your pain and other symptoms, and your quality of life”, with the answer marked by either “yes” or “no”. Participants who answer “no” will be asked to complete the second single-item question, relating to treatment failure: “Would you consider your current state as being so unsatisfactory that you think treatment has failed?”, with the answer marked by “yes” or “no”.

Further, participants will be followed actively by a weekly questionnaire delivered via email as a secure online link with standardised questions about pain and symptoms, amount and type of painkillers, days of being sick or on sick-listing, concomitant treatment during the past week, and potential adverse events.

#### Baseline participant characteristics

General demographic information will include age, sex, civil status, educational level, employment, previous treatment, pain medication, and disease history. Anthropometric measurements include weight and height. To measure physical activity level, the short version of the International Physical Activity Questionnaires (IPAQ) will be used to collect information on time spent in walking and physical activity at moderate and vigorous intensity in four domains: work, transportation, housework/gardening, and leisure time [36, 37]. Participants will be asked to indicate the amount of time spent in physical activity in the past 7 days in relation to frequency (days) and duration (hours or minutes) of the activities.

### Participant timeline {13}

Participants will undergo a structured time schedule including the intervention and assessments (Fig. 2).

### Sample size {14}

Sample size calculation is based on the between-group difference in the mean change scores of WOSI total from baseline to the 16-week follow-up. Based on previous studies on patients with HSD/hEDS, we expect a mean baseline WOSI total of 1050 points [8, 22]. The study will be powered to detect a between-group difference equal to or greater than a previously reported clinically important change of 252 points [40, 63], with an SD for change from baseline to the 16-week follow-up of 350 points [16, 22]. We expect both groups to experience a clinically relevant improvement, seen as a 48% improvement in the HEAVY group (equal to 504 points with an expected baseline mean score of 1050 points) comparable with effects of previous interventions [16, 18, 22, 34, 64, 65] and 24% improvement in the LIGHT group [18] (equal to 252 points with an expected baseline mean score of 1050 points). With a two-sided significance level of 0.05 and 90% power, a sample size of 42 per group is required to detect a statistically significant difference. We decided to enrol 50 patients per group to account for a conservatively estimated dropout of 16% [16, 18]. If 100 patients are not included within 24 months (01 Apr 2019 to 31 Mar 2021), a stopping rule will be applied as soon as a minimum of 76 patients have been included, equal to a power of a minimum of 80%, including 16% dropout.

### Recruitment {15}

Patients will be recruited from April 2019 to March 2021 by general practitioners from local medical clinics and eight physiotherapy clinics in the cities of Odense, Middelfart, and Esbjerg in Denmark. The general practitioners and physiotherapists will receive information about the project, the patient group, and the eligibility criteria to be able to identify and administer the online pre-screening questionnaire to potential patients with HSD/hEDS and long-lasting shoulder complaints in their clinics. All participants had a medical referral to physiotherapy treatment. To achieve adequate enrolment, we have included additional recruitment sites as was apparent to be necessary during the feasibility study as well as social media announcements, and the 2-year recruitment period is anticipated to be adequate time to recruit the required sample size.

## Assignment of interventions: allocation

### Sequence generation {16a}

The allocation sequence will be computer-generated with permuted block randomisation, set up by a data manager outside the project. Participants will be randomly assigned to either HEAVY or LIGHT with a 1:1 allocation ratio.

### Concealment mechanism {16b}

Randomisation is performed automatically in REDCap by the project manager. To ensure allocation concealment, the principal investigator, outcome assessors, and project manager will be blinded to block sizes and unaware of the next assignment in the allocation sequence.

### Implementation {16c}

All eligible patients who give consent for participation and who fulfil the inclusion criteria will be appointed a time for baseline testing. Immediately following the baseline testing session, the project manager will complete the randomisation and reveal the unique group allocation to the patient. Randomisation will be conducted without any influence of the principal investigators, outcome assessors, or treating physiotherapists. The project manager will contact the treating physiotherapist to make sure that all practical aspects run smoothly, including appointment bookings.

## Assignment of interventions: blinding

### Who will be blinded {17a}

The principal investigator and the four outcome assessors will be kept blinded from group allocation.

The participants will be kept blind to treatment allocation by being provided with minimal information about the content of the two exercise interventions and the study hypotheses; the participants will be informed that the study compares two different exercise protocols including safe exercises aimed at increasing the function of the shoulder muscles, but they will not be told of the direction of our hypothesis. During the follow-up testing, participants will be encouraged not to disclose or discuss with the outcome assessors what type of exercises they have performed. The treating physiotherapists responsible for delivering both interventions will not be blinded to which treatment the participants have been allocated to. The treating physiotherapists will be blinded to baseline and follow-up testing results. All pre-defined analyses will be performed by an epidemiologist (EB) blinded to group allocation.

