**Methods:**

A superiority, parallel group, randomised controlled trial will be conducted with 100 patients from primary care with HSD/hEDS and shoulder complaints (persistent pain and/or instability) for more than 3 months. Participants will be randomised to receive HEAVY (full range of motion, high load) or LIGHT (neutral to midrange of motion, low load) strengthening programme three times weekly with exercises targeting scapular and rotator cuff muscles. HEAVY will be supervised twice weekly, and LIGHT three times during the 16 weeks. The primary outcome will be between-group difference in change from baseline to 16-week follow-up in the Western Ontario Shoulder Instability Index (WOSI, 0-2100 better to worse). Secondary outcomes will include a range of self-reported outcomes covering symptoms, function, and quality of life, besides clinical tests for shoulder strength, laxity/instability, and proprioception. Outcome assessors will be blinded to group allocation. Participants will be kept blind to treatment allocation through minimal information about the intervention content and hypotheses. Primary analyses will be performed by a blinded epidemiologist.

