### Trial design {8}

This study is an assessor-blinded, multicentre, randomised, controlled superiority trial with a two-group parallel design, comparing HEAVY with LIGHT (considered standard care in Denmark) (Fig. 1). Participants will be randomised with a 1:1 allocation ratio, without an option to cross over. The primary endpoint will be the between-group difference in change in self-reported shoulder function from baseline to 16-week follow-up.

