### Intervention description {11a}

#### Treating physiotherapists

The treating physiotherapists responsible for delivering the interventions have undergone a 3-h practical and theoretical education programme, supported by an exercise manual provided by the principal investigator (Supplementary files 3 and 4). The same treating physiotherapists will deliver exercise programmes for both groups, and they will be instructed to treat all participants with the same degree of rigour, enthusiasm and optimism. An envelope with exercise manuals for the participant and the physiotherapist will be delivered to every participant to prevent the treating physiotherapists from giving exercises to the wrong group by mistake. The same physiotherapist will supervise the participant through the intervention period, and if needed due to absence, another physiotherapist from the same physiotherapy clinic will take over. In vacation periods, participants will be encouraged to exercise on their own three times weekly, with adjustable dumbbells provided by the project team to the HEAVY group.

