## Data collection and management

### Plans for assessment and collection of outcomes {18a}

Before starting data collection, the outcome assessors will receive comprehensive education by the principal investigator in the assessment protocol over two sessions, to agree on standardised procedures for all objective outcome measurements. For all participants, data collection will be performed at baseline and at the 16-week follow-up on self-reported outcomes and objective measurements, and at the 12-month follow-up on self-reported outcomes via email as a secure online link (Fig. 2). Participants will complete the self-reported measurements directly into REDCap, and outcome assessors will enter the data in REDCap from their clinical tests and objective examinations at completion of those assessments. Data collection will be performed in an undisturbed room. At supervised exercise sessions, the treating physiotherapists will register the data concerning the exercise session (pain level, load, progressions, repetitions, sets, adverse events, and pain level before and after the session) in a printed exercise logbook, and at home-based sessions, the participants will fill out the exercise logbook. Data from the weekly questionnaire are entered by the participants directly into REDCap. All forms were designed by the Steering Committee.

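### Participants are described as blind to allocation although the allocation is revealed to them, so the self-reported primary outcome is not blinded to allocation

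*Protocol article*

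**What the plan says.** The claim of participant blinding appears twice in the protocol article. The Methods part of the abstract states: "Participants will be kept blind to treatment allocation through minimal information about the intervention content and hypotheses". The section on who will be blinded {17a} states: "The participants will be kept blind to treatment allocation by being provided with minimal information about the content of the two exercise interventions". That section adds that participants are told two safe exercise protocols are being compared, but not which one is expected to do better.

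The implementation section {16c} describes what happens right after the baseline session: "the project manager will complete the randomisation and reveal the unique group allocation to the patient".

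On the outcome, the article says: "The primary outcome is self-reported shoulder function measured using the WOSI total score". On how it is recorded {18a}: "Participants will complete the self-reported measurements directly into REDCap". The trial design section {8} uses a narrower label: "This study is an assessor-blinded, multicentre, randomised, controlled superiority trial".

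**The concern.** Allocation cannot be both revealed to the participant and withheld from the participant. The contradiction matters because the participant is the rater of the primary outcome. With a self-reported scale, a rater who knows the allocation can let expectation affect the answers, and blinding the physiotherapist assessors does nothing about that. Nor do the blinded analyst and the blinded interpretation promised in the statistical methods section {20a}, because they act after the answers have been given.

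At stake is what the trial may claim. If the wording stands, the trial report can credit the primary comparison with participant blinding that the design does not provide.

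**Working it through.** **1. Is allocation known to participants?** The relevant places in the protocol article, side by side:

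| Place | What it implies |
|---|---|
| Abstract; {17a} | Participants do not know their allocation |
| Implementation {16c} | Participants are told their allocation after baseline |
| Treating physiotherapists | Participants hold the programme manual: "An envelope with exercise manuals for the participant and the physiotherapist will be delivered to every participant" |
| HEAVY and LIGHT descriptions, Tables 1 and 2 | One arm trains with dumbbells at a clinic and at home; the other does isometric and later light-band work at home |
| {17a}, later sentence | Participants are asked not to discuss their exercises with the assessors, so they are assumed to know them |
| Unblinding {17b} | After a serious adverse event, participants are encouraged to describe the type and intensity of their exercises to their general practitioner |

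Contact time differs openly as well: "HEAVY will be supervised twice weekly, and LIGHT three times during the 16 weeks". As planned, that is 2 × 16 = 32 supervised sessions against 3. Only the first row supports blinding to allocation.

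**2. What stays masked?** By {17a}, the direction of the hypothesis and detail on the content of the two programmes. That is masking to the hypothesis, not to the allocation.

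**3. Which outcomes are affected?** By {18a}, participants enter the self-reports and the outcome assessors enter the clinical tests and objective examinations. WOSI falls on the participants' side, together with its subscales, pain and symptom ratings, PSFS, fatigue, COOP/WONCA, TSK-11, EQ-5D-5L and GPE. Strength, range of motion, proprioception and the laxity and instability tests fall on the blinded assessors' side. The 12-month follow-up collects self-reported outcomes only, so no assessor-blinded measure is available at that time.

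**4. Does any planned figure depend on participant blinding?** The sample size section {14} gives a difference of 252, an SD of 350, two-sided alpha of 0.05 and 90% power.

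- n per group = 2 × (1.960 + 1.282)² × 350² / 252² = 2 × 10.51 × 1.929 = 40.5, so 41 by the normal approximation.
- The t-test version gives 41.5, so 42, as stated.
- With 16% dropout, 42 / 0.84 = 50 per group, as stated.

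The figures reproduce, and blinding enters none of them.

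**5. How sensitive is the comparison to a reporting difference?** The document gives no size for such a difference, so the values of b below are assumptions for illustration. Take 42 per group, SD 350, no true effect, and an average reporting difference b between the arms in either direction. Ignore covariate adjustment and clustering. Then SE = 350 × √(2/42) = 76.4 and

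P(reject) = 1 − Φ(1.96 − b/SE) + Φ(−1.96 − b/SE).

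| Assumed b (WOSI points) | b / 252 | P(reject) |
|---|---|---|
| 0 | 0% | 5% |
| 50 | 20% | 10% |
| 100 | 40% | 26% |
| 126 | 50% | 38% |

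This shows only that a reporting difference well below the target difference would matter if it occurred. It does not show that one will occur.

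**The case against.** The strongest reply is that this is loose terminology. The sentence in {17a} discloses its own mechanism, namely limited information and an undisclosed hypothesis, and nearby text plainly assumes that participants know their exercises. On that reading, blind means unaware of which programme is expected to win. The trial design section calls the trial assessor-blinded only, and no section says that assessor blinding covers WOSI. The section on the choice of comparators {6b} already concedes that the extra supervision in HEAVY may bring contextual effects and attention bias that cannot be accounted for. In an exercise trial, participants inevitably know what they do.

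Most of this limits the point without removing it. Twice the article names allocation as the thing participants are blind to, and {16c} says allocation is revealed; a charitable reading does not reconcile those words. The concession in {6b} concerns unequal attention, not knowledge of allocation, and leaves the blinding claim uncorrected. The strengths and limitations section does not mention it.

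Three stronger readings are tempting, and the document does not support them:

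- A reader might infer that participants have no protection at all. Masking of the hypothesis remains and may reduce expectation bias.
- A reader might infer that the protocol offers participant blinding as its stated safeguard against reporting bias. It never makes that link.
- A reader might infer that the primary result will be biased towards HEAVY. Participants are not told the hypothesis, and the background section reports clinicians' hesitation about heavy exercise on safety grounds, so the direction cannot be taken for granted.

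**Conclusion.** The claim that participants are blind to allocation is wrong as written. It is contradicted by the implementation section and by the visible differences between the programmes. WOSI and all other self-reported outcomes are therefore not blinded to allocation, at 16 weeks and at 12 months; only the objective tests are assessor-blinded.

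The size and direction of any resulting bias cannot be estimated from the document, and the illustrative rejection probabilities rest on assumed values. No planned number, randomisation step or analysis changes. What changes is the claim the trial may make about bias in its primary comparison. The conclusion rests on reading {16c} literally, which the rest of the protocol supports.

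**What to change.** - Abstract, {16c} and {17a}: reconcile the three places so that they say participants are told their allocation, are not blinded to it, and are masked only to the study hypothesis.
- Trial design {8}: state that assessor blinding applies to the objective tests measured by the physiotherapists.
- Choice of comparators {6b} or strengths and limitations: add that WOSI and the other self-reported outcomes are open to expectation and reporting bias because participants know their allocation, and that this will be acknowledged when the primary result is interpreted.

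The cost is a few sentences; the downside is that the stated blinding becomes less favourable.

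Two further remedies might suggest themselves, but neither is needed. Reading WOSI beside the strength results would not validate the self-reports, because strength is a direct target of HEAVY and maximal voluntary contraction depends on effort. Adding an expectation question after allocation would miss participants already past their first week: recruitment began on 1 April 2019 and this protocol version is dated 6 April 2020.
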